### Randomization Method

Randomization will occur with randomly generated computer lists held at the Duke site. All patients will be stratified by the following characteristics in block randomization:

Subtype of depressive disorder (bipolar type II vs. unipolar), presence or absence of rapid cycling, and duration of current MDE (< vs. > 3 months). These features may be unequally distributed in a small (<50) randomized study and could lead to high placebo response if type II, rapid cycling, or short duration episodes are overrepresented in the placebo group. Stratification will ensure control of these factors.

1. Outcome Measures and Planned Analyses

The a priori primary outcome measure will be change from baseline in MADRS scores in the acute phase. A priori secondary measures will be change from baseline in HAM-A, MRS, and other scores. The primary analysis for the acute phase between group effect size (for ziprasidone vs. placebo) will be obtained by unpaired t-test comparison and by mixed effects regression modeling. A priori subgroup analysis in rapid cyclers versus nonrapid cyclers, unipolar vs. bipolar subtypes, and shorter versus longer duration episodes, is also planned.

1. Definition of Evaluable Subject (Safety and Efficacy)

Subjects will be defined as able to be evaluated by two methods. The primary method will be an intent-to-treat analysis, including those who discontinue drug due to lack of efficacy or due to side effects. The secondary method will be completer analysis.

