###### STATISTICAL EVALUATION

1. Power Analysis

A power analysis was conducted. With a goal for =0.20, and two-tailed =0.05, the pilot studies previously conducted for the mania registration trials suggested that a mean change in MADRS scores were 20 points improved with ziprasidone compared to placebo. Given the few patients in the placebo arm, we conducted this power analysis with a smaller expected effect size, using a high projected mean difference of 10 points, and a low projected mean difference of 5 points. Based on the available pilot data, a projected standard error of the mean difference was assumed to be range from equivalent to the mean difference to twice as much as the mean difference (5-15 points). Using an internet-based power analysis software program, we conducted the power analysis noted in the table.

To assess various levels of effect size, power, and standard deviation, a sensitivity analysis was conducted (Table). As indicated by the table, if the mean difference is small and the standard deviation is large, then very large samples would be needed. However, if the same or larger effect was seen with somewhat larger standard deviation, the total sample size required would range from 26 to 138 patients. Thus, unless the true mean difference is quite minimal, a sample size in that range should have a good chance of detecting a real effect.

Table. Sensitivity analysis for sample size calculation

| Sample size (per arm) | Effect size (Mean difference in MADRS) | Standard deviation within each group | Power |
| --- | --- | --- | --- |
| 13 | 5 | 5 | .80 |
| 50 | 5 | 10 | .80 |
| 69 | 5 | 10 | .90 |
| 112 | 5 | 15 | .80 |
| 30 | 10 | 5 | .90 |
| 13 | 10 | 10 | .80 |
| 18 | 10 | 10 | .90 |
| 29 | 10 | 15 | .80 |
| 5 | 20 | 10 | .90 |

Therefore, a sample size of about 100 patients should be optimal for this study. This would be best accomplished in 4 sites, with a goal of accrual of 25 patients per site. At an average recruitment of about 2 patients per month, this could be achieved in one year of recruitment.

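### The single primary comparison is assigned to both an unpaired t-test and a mixed model, with no rule for which decides or at which visit, and the t-test adjusts for neither baseline MADRS nor the stratification factors

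*Protocol*

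**What the plan says.** Under Statistical Evaluation, the paragraph on outcome measures and planned analyses sets the endpoint: "The a priori primary outcome measure will be change from baseline in MADRS scores in the acute phase". For the primary analysis it says that the effect size for ziprasidone versus placebo "will be obtained by unpaired t-test comparison and by mixed effects regression modeling". The two methods are joined by a plain conjunction. No sentence ranks them, and neither a decision visit nor any covariate is named.

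The acute phase lasts 6 weeks (Study Design), and MADRS is scored at screening and at Weeks 0 to 6 (Study Visit Schedule). Each patient can therefore contribute up to six post-baseline changes.

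Randomisation is stratified by depressive subtype, rapid cycling and duration of the current episode (Randomization Method). The reason given is that imbalance in these features could raise placebo response, so the Protocol itself treats them as likely to be prognostic.

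On the analysis set: "The primary method will be an intent-to-treat analysis, including those who discontinue drug due to lack of efficacy or due to side effects". Then: "The secondary method will be completer analysis". The Power Analysis works at two-tailed 0.05.

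**The concern.** A confirmatory comparison needs one test, one contrast and one error rate. Here two methods carry the same claim, and they need not estimate the same quantity. An unpaired t-test takes one change score per patient. A mixed model of weekly scores can deliver a Week 6 difference, an average over visits or a difference in slopes, and the wording of the endpoint does not choose among these.

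If one p-value falls below 0.05 and the other does not, the Protocol does not say whether the trial succeeded. Whoever settles that after unblinding is choosing between two known results.

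The second issue is precision. Having stratified on three factors thought to affect outcome, the trial gives equal standing to a test that uses none of them and that uses baseline only by subtraction.

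**Working it through.** **The plan's own benchmark.** The Protocol gives no figure for this point. The row of its sample-size table behind a total of about 100 is 50 per arm, difference 5, SD 10, power 0.80. For an unadjusted two-sample comparison:

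- n per arm = 2(z_alpha + z_beta)²(SD/difference)²
- two-sided 0.05: 2(1.960 + 0.842)² × 4 = 63 per arm
- one-sided 0.05: 2(1.645 + 0.842)² × 4 = 50 per arm

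So 50 per arm has 70.5% power two-sided (69.7% by exact t). That shortfall is a separate matter. It is used here only as the reference for the t-test.

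**Type I error if either test may decide.** Were the two tests independent, the rate would be 1 − 0.95² = 9.75%. They use the same data and are strongly correlated, so this is only a reference ceiling. Simulation gives realistic values.

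*Simulation 1* (4,000 trials per scenario, 50 per arm). Assumed inputs, none of them in the Protocol:

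- SD rising from 6 at baseline to 10 at Week 6; correlation 0.6^(lag/3), so 0.6² = 0.36 between baseline and Week 6
- SD of Week 6 change = √(36 + 100 − 2 × 0.36 × 6 × 10) = √92.8 = 9.6, close to the Protocol's 10
- effect growing linearly to its Week 6 value
- each stratification factor worth 0 or 2 points at Week 6
- dropout of about 0, 20 or 30%, more likely with worse scores

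The t-test used the last observed change. The mixed model gave the Week 6 contrast adjusted for baseline and strata, with its covariance treated as known. Ranges span the two settings for the strata.

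| True difference | Dropout | t-test rejects | Mixed model rejects | Either rejects | They disagree |
|---|---|---|---|---|---|
| 0 | 0% | 4.6-5.0% | 4.8-5.1% | 6.0-6.5% | 2.6-2.9% |
| 0 | 20% | about 4.5% | 4.6-4.9% | 5.8-6.1% | 2.5-2.8% |
| 0 | 30% | 4.7% | 4.6-4.7% | 6.2-6.3% | 3.1-3.2% |
| 5 | 0% | 72.5-72.8% | 76.1-76.4% | 78.6% | 8.2-8.3% |
| 5 | 20% | 67.5-68.9% | 68.1-68.2% | 72.7-73.7% | 9.8-10.3% |
| 5 | 30% | 63.6-65.8% | 62.2-63.3% | 68.3-70.3% | 10.8-11.5% |

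The Monte Carlo standard error at a rate of 10% is √(0.1 × 0.9/4000) = 0.5 percentage points.

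*Simulation 2* (no dropout, baseline SD 5, SD of change about 9-10; 20,000 null trials and 8,000 with a 5-point effect) varied what the mixed model targets. Each test alone rejected in about 4.8% of null trials. Either rejected in 6.4% when the model tested a slope and in 6.9% when the average over Weeks 1-6 was tested. With a 5-point effect, the t-test and the slope model disagreed in about 10%.

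**What the missing rule is worth.** Both reject = t-test + mixed model − either. With no dropout and no stratum effect this is 72.75 + 76.10 − 78.55 = 70.3%. The same trial thus succeeds 70.3% of the time if both must reject and 78.6% if either suffices.

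**Adjusting for baseline against subtracting it.** With k = baseline SD / Week 6 SD and correlation ρ, the ratio of adjusted to change-score variance is (1 − ρ²)/(1 + k² − 2ρk).

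| ρ | k = 1 | k = 0.5 |
|---|---|---|
| 0.3 | 0.65 | 0.91/0.95 = 0.96 |
| 0.5 | 0.75 | 0.75/0.75 = 1.00 |
| 0.7 | 0.85 | 0.51/0.55 = 0.93 |

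The gain therefore runs from nothing to 35% of variance. At 50 per arm, difference 5 and SD of change 10, the k = 1 column gives power of 87%, 82% and 77% against 70.5% unadjusted.

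**The case against.** **The analysis plan is not shown.** Model parameterisation, covariate lists and imputation rules commonly sit in an SAP, and their absence from a protocol is no fault. That stands for the detail. It does not cover the main point, because the Protocol has itself given primary status to two methods.

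**The inflation is small and conditional.** The conjunction could mean that both must reject, in which case type I error cannot exceed 5%. Even on the looser reading it is 6-7%. This stands, and the undefined conclusion is the more serious harm.

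**The precision gain may be slight.** If the baseline SD is half the Week 6 SD, adjustment saves only 0-7% of variance. At 30% dropout in Simulation 1, the last-observation t-test had slightly more power than the adjusted mixed model. This also stands, so the power of 77-87% should not be presented as the expected benefit.

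**Stronger readings a reader might infer, which the Protocol does not support:**

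- *The t-test ignores baseline MADRS.* It does not: the outcome is a change score, so baseline is subtracted, though not adjusted for.
- *The t-test ignores dropouts or contradicts intent-to-treat.* The primary set includes discontinuers, and completers are a separate secondary analysis. The Protocol is silent on what value a discontinued patient contributes, and a t-test with an imputation rule is compatible with that set. The choice matters (at 30% dropout, power was 64-66% with the last observation and 52-54% using only patients seen at Week 6), but it may be left to the SAP.
- *Stratification is wrongly credited.* "Stratification will ensure control of these factors" follows a sentence about unequal distribution between arms, so it means balance by design, which is a fair use of the word.

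**Conclusion.** The point holds in limited form. The Protocol declares two primary methods for one comparison, with no ranking, no joint rule and no decision visit. With 50 per arm and a true 5-point effect, the two give different answers in roughly 8-12% of trials. In those trials the conclusion would rest on a choice that could be made after seeing the data. Type I error is about 6-7% if either may decide, and is not inflated if both must reject.

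The unpaired t-test also leaves baseline MADRS and the three stratification factors unadjusted. Its standard error is too large to the extent that these are prognostic. For baseline the cost is 0-35% of variance over the assumed range; for the factors the Protocol gives nothing from which to size it.

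The absence of a decision rule is read directly from the text. The percentages depend on assumed SDs, correlations, effect shape and dropout, which the Protocol does not supply.

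**What to change.** Replace the sentence on the primary analysis with one that names a single method and a single contrast:

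- **Primary analysis:** repeated-measures mixed model of MADRS change at Weeks 1-6 in all randomised patients, with treatment, week, treatment-by-week, baseline MADRS and the three stratification factors.
- **Decision contrast:** the treatment difference at Week 6, two-sided 0.05. No other model term or visit decides the trial.
- **Unpaired t-test:** supportive only, reported beside the primary result and unable to overturn it.

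The factors entered should be those actually used to randomise. The Study Design schematic shows a different subtype split (type I versus type II/NOS) from the text (type II versus unipolar), so the two should be aligned first.

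The cost is one paragraph, settled before unblinding. Weekly MADRS, baseline MADRS and the stratification factors are already collected, and no visit, assessment or patient is added.

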### Visit-Specific Treatment and Evaluation Sequence

Visits will be planned to occur at the screening visit and weeks 0, 1, 2, 3, 4, 5, 6. Research scales will be administered at each visit. For a detailed description of which scales are administered per visit, please see “XIV. Study Visit Schedule” on page 21. No research procedures will be performed without a patient first signing an informed consent. Laboratory tests, consisting of CBC with differential, biochemistry profile, ECG and urine pregnancy test, will be conducted prior to the acute phase, prior to the continuation phase, and at study termination. Physical examination and vital signs will be assessed at study entry and termination visits. Patient termination will occur if the patient experiences a worsening of MADRS scores greater than 30% above the baseline score in two successive visits or if MRS > 20 in two successive visits, or based on clinician judgment or patient preference.

1. Concomitant Medication and Therapy

All allowed concomitant medications will be unchanged throughout the study.

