### Quality Assurance Audits

Charts will be made available as requested to the sponsor, the participating site IRBs, and the FDA or other federal regulatory bodies for quality assurance purposes.

1. Study Discontinuation/Termination

Patients will be discontinued from the study for the following reasons:

1. 30% worsening of MADRS compared to baseline on two successive visits
2. MRS > 20 in two successive visits
3. Worsening of suicidal ideation (SI) as determined by MADRS suicide item  3 in two successive visits.
4. Clinical worsening sufficient to require hospitalization or other medication interventions in the judgment of the treating psychiatrist
5. Patient noncompliance with medications or appointments
6. Patient preference

After study termination, subjects who do well will receive Geodon. Subjects who do not do well will have the option of receiving Geodon. The blind will be broken only if there is a medical emergency.

D. Serious Adverse Event Reporting

For those studies where the principal investigator is required to report serious adverse advents (SAEs) to Pfizer, the investigator must use the enclosed Serious Adverse Event Fax Cover Sheet together with the FDA’s MEDWATCH form FDA 3500A (for mandatory reporting) which can be downloaded at [www.FDA.gov](http://www.FDA.gov/).

Reporting of Serious Adverse Events: Within 24 hours of first awareness of the event (immediately if the event is fatal or life-threatening), Principal Investigator will report to Pfizer by facsimile any Serious Adverse Event (“SAE,” as defined below) that occurs during the SAE reporting period (as defined below) in a Study subject assigned to receive the Pfizer Product (see Section 5, Pfizer Product). Principal Investigator will report such SAEs using an FDA MEDWATCH form and the *Serious Adverse Event Fax Cover Sheet* provided by Pfizer. SAEs should be reported as soon as they are determined to meet the definition, even if complete information is not yet available. SAEs will be reported to the Tufts Medical Center IRB on the same schedule as the study sponsor.

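### Minor: the completer analysis named as the secondary method, for safety as well as efficacy, selects patients partly on the outcome and is a poor check on the intent-to-treat result

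*Protocol*

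**What the plan says.** The Protocol's Statistical Evaluation section has a subsection defining the evaluable subject, and its heading names both safety and efficacy. It gives two methods. On the first it says: "The primary method will be an intent-to-treat analysis, including those who discontinue drug due to lack of efficacy or due to side effects". On the second: "The secondary method will be completer analysis". It names no separate safety set and does not define a completer further.

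Two other places decide who can complete:

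- Visit-Specific Treatment and Evaluation Sequence ends participation for "worsening of MADRS scores greater than 30% above the baseline score in two successive visits", for MRS above 20 at two successive visits, "or based on clinician judgment or patient preference".
- Study Discontinuation/Termination lists "30% worsening of MADRS compared to baseline on two successive visits", the same MRS rule, the MADRS suicide item at two successive visits, and "Clinical worsening sufficient to require hospitalization or other medication interventions in the judgment of the treating psychiatrist". It also lists noncompliance and patient preference.

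Change in MADRS is the primary outcome, and change in MRS is a named secondary outcome.

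**The concern.** A secondary analysis set is useful if it tests whether the primary result depends on a debatable assumption. A completer set does this badly here, because membership is decided after randomisation and partly by the scale being compared. If the drug works, more placebo patients should meet the worsening rule. Their poor outcomes then leave the placebo mean, and the difference between arms shrinks.

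For safety, the set removes those who stopped because of side effects. These are the patients a tolerability comparison most needs.

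If the completer and intent-to-treat results disagree, the reader cannot tell selection from a drug effect. If they agree, little has been learned.

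**Working it through.** **No plan figure to reproduce.** The protocol states no dropout rate, completer count or completer effect. The check is therefore an argument from the text, with a simulation to show size.

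**From the text.**
1. Exit depends on MADRS (worsening rule, suicide item), on MRS and on clinical worsening. Completion is thus a function of outcomes after randomisation.
2. The intent-to-treat set is described as "including those who discontinue drug due to lack of efficacy or due to side effects", so the completer set is the one without them. The number of side-effect discontinuations in it is zero in both arms, whatever the true rates.
3. The Blinding and Controls section lets patients who do not finish the six weeks enter the open-label courtesy trial after the baseline visit. A patient doing poorly therefore has a reason to leave early. This makes exit beyond the 30% rule plausible but does not quantify it.

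**Efficacy, the 30% rule alone.** From the protocol: 50 per arm (100 patients, 1:1), differences of 5 and 10, SDs of 5, 10 and 15 (power table), weekly visits, and exit when MADRS exceeds 1.3 × baseline at two successive visits. Assumed: baseline MADRS 28, mean placebo change −8 (also −4), and the shape of the trajectories.

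- Random-slope trajectories, residual SD 4, SD of week-6 change 10, means −8 and −13, 400,000 patients per arm. The rule removes 3.1% on placebo and 0.9% on drug. The difference is 4.99 in all patients and 4.56 in completers, a shift of 4.99 − 4.56 = 0.43.
- Visits correlated at 0.6, baseline SD 5, 200,000 per arm, with side-effect dropout unrelated to MADRS:

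| True difference | SD | Placebo change | All patients | Completers |
|---|---|---|---|---|
| 5 | 5 | −8 / −4 | 5.02 / 5.04 | 4.98 / 4.95 |
| 5 | 10 | −8 / −4 | 4.98 / 5.01 | 4.57 / 4.47 |
| 5 | 15 | −8 / −4 | 5.03 / 5.04 | 4.31 / 4.18 |
| 10 | 10 | −8 / −4 | 10.01 / 9.98 | 9.35 / 9.06 |
| 0 | 10 | −8 / −4 | −0.01 / −0.01 | −0.05 / −0.01 |

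At SD 10, true difference 5 and placebo change −8, the runs under different side-effect dropout rates give 4.57 to 4.68. With the random-slope result this is about 4.6-4.7. A placebo change of −4 gives about 4.5. At SD 5 the loss is under 2%. At SD 15 it is 14% (0.72/5.03) to 17% (0.86/5.04).

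**Efficacy, extra exit.** In the random-slope model, 30%, 50% or 70% of patients with a change above −2 at week 4 also leave. Total exit is then 12-24% on placebo and 6-13% on drug. The completer difference is 4.37, 4.18 and 3.92. Allowing for other trajectory assumptions, the range is about 3.9-4.5, a loss of 10% (0.5/5) to 22% (1.1/5). These exit rates are assumed.

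**Scale.** With 50 per arm and SD 10, the standard error of the difference is 10 × √(2/50) = 2.0. The shift of 0.43 from the rule alone is about 0.2 standard errors. It comes from about 50 × 0.031 = 1.6 placebo patients and 50 × 0.009 = 0.5 drug patients.

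**Safety, illustration.** Assume a true side-effect excess on drug of 19 percentage points in all patients:

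| Side-effect dropout, drug vs placebo | Excess among completers |
|---|---|
| 5% vs 5% | 20 points |
| 10% vs 5% | 17 points |
| 15% vs 5% | 14 points |
| 20% vs 5% | 10 points |

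The dilution appears only when more patients leave the drug arm for side effects.

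**The case against.** The best defence is that the plan already does the right thing first. Under the same heading, intent-to-treat is the primary method and expressly keeps patients who stop for lack of efficacy or side effects. If the heading carries the completer set into safety, it carries intent-to-treat there too. The planned analyses already include mixed effects regression. A secondary completer analysis is customary, and finer detail may sit in a statistical analysis plan that is not at hand. The safety reading rests on the heading alone, since no safety table is described. The shift from the 30% rule is small against a standard error of 2.0, and the larger figures need assumed dropout. In these scenarios the bias understates benefit and does not create a false positive.

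Most of this stands, and it is why the point is minor. It does not rescue the completer set as the one named secondary method: that choice is fixed in the protocol, and a better one is available.

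Three stronger readings are tempting, and the text does not support them:

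- *Completers are patients who did not worsen.* The rule needs about 30% worsening at two successive visits. Patients with smaller, isolated or last-visit worsening can complete.
- *The stopping rules remove patients with side effects.* The discontinuation list has no such item. Their absence follows from what a completer is and from the evaluable-subject wording. Clinician judgment or patient preference is the route out.
- *Both comparisons are certainly biased.* Size and direction depend on dropout by arm, which the protocol does not give, and in some of the cases above the bias is nil.

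**Conclusion.** The point holds as a minor one. The protocol's only named secondary method conditions on completing, and completing depends on MADRS, MRS, clinical worsening and, through the meaning of the term, tolerability. The completer comparison is open to selection bias and is a poor check on the intent-to-treat result.

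At a true difference of 5 and SD 10, the illustrated loss is about 0.3-0.4 MADRS points from the 30% rule alone (placebo change −8), and about 0.5-1.1 if poor responders also leave. Both figures rest on an assumed baseline of 28 and assumed trajectories, and the second also on assumed exit rates. The loss from the rule alone is negligible at SD 5, larger at SD 15 and absent with no treatment effect.

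A reader might infer that the trial's main efficacy or safety conclusion is compromised. It is not: the primary intent-to-treat analysis keeps the patients whom the completer set drops.

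**What to change.** Change the evaluable-subject subsection in three places:

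1. Safety: report it only in all patients who took study drug, and drop the completer set.
2. Efficacy: replace the completer analysis as the secondary method with a sensitivity analysis that keeps all randomised patients. Use the mixed model already planned, on all observed visits, plus a version assuming worse outcomes after dropout. The mixed model suits exits under the 30% rule, because that rule acts on MADRS scores that have been recorded. The second version addresses exits through judgment or preference, whose reasons may not show in the recorded scores.
3. If completer means are shown at all, label them descriptive.

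The cost is a few lines of text, one extra model run and the loss of a customary supportive table. No visit, stopping rule or sample size changes.
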